### 1.1 Reference number

CIV-23-07-043416

### 1.2 Amendments from prior versions of the CIP

N/A

### 1.3 Abbreviations and acronyms

BCT- Behavior Change Technique

CRF- Case Report Form, a list of the variables that will be collected and saved for research purpose

IB- Investigator's Brochure, a protocol for the investigators and health coaches

ISI- Insomnia severity Index

MARS- Mobile Application Rating Scale

OLBI- The Oldenburg Burnout Inventory

KEDS- The Karolinska Exhaustion Disorder Scale

SUS- System Usability Scale

S-GSE General Self-Efficacy scale

RCT- Randomized Controlled Trial

RTCQ- Readiness To Change Questionnaire

WHO-5- World Health Organisation Well-Being Index

#### **Funding**

Diabetesfonden (Dnr DIA2021-666)

Sophiahemmet Ideell Förening

Mälardalsområdets forskarskola

Additional funding has been applied for from e.g. Forte, AFA Försäkring

## **1.6 Overall synopsis of the clinical investigation**

*Study design:* Post-market observational clinical investigation with a control group (a quasi-experimental study). The project also includes implementation and longitudinal studies.

*Inclusion criteria (intervention arms):* Adults  $\geq 18$  years who sign up for the service LongLife Active using BankID for identification, and consent to the research study.

*Inclusion criteria (controls):* Adults  $\geq 18$  years.

- *Exclusion criteria (intervention arms):* Individuals who are discharged from the app due to refracting the terms of the service will be excluded. Subjects scoring  $>70$  on well-being or subjects who appear as friends, colleagues, or family with anyone in the research or owner group will be excluded from the primary analyses.
- *Exclusion criteria (controls):* Age  $\leq 17$  years. Is currently using a digital product or any other kind of support for behavior change (e.g. Livsstilsverktyget, Health Integrator, Weight Watchers). Is found to be a user of LongLife Active. Subjects scoring  $>70$  on well-being or subjects who appear as friends, colleagues, or family with anyone in the research or owner group

will be excluded from the primary analyses.

*Number of subjects:* Intervention: 5000, Controls: 200

*Duration of the intervention:* the subjects will be followed up to 24 months.

*Follow-ups:* 3, 6, 12, 18, and 24 months

*Objectives:* The aim of this project is to evaluate the effectiveness of an individually tailored digital service aimed to support healthy habits on well-being among the adult population compared to a control sample of the general population.

Secondary objectives are to describe the internalization of the digital service, to evaluate the impact of the digital service on reaching self-identified goals, behavior change, and mental health, and to explore predicting and mediating factors for responses.

*Primary endpoint:* Well-being at 6 months

*Secondary (intermediate) endpoints:* Achieving self-identified goals, dietary and physical activity habits, and mental balance.

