### 4.2 Anticipated adverse device effects

Adverse effects of digital support for behavior change are not obvious, and none have been reported in the scientific literature as far as we are aware. A systematic review including 113 RCTs investigating healthy diet and physical activity counselling reporting on adverse effects found no evidence for greater harm in the intervention versus the control group (33). Nevertheless, there are some identified concerns associated with the use of digital services for behavior change. The main risks that concern end-users are related to data security and confidentiality, reliability of the device,

and trustworthiness of the manufacturer (2, 23). Demotivation, self-confidence, self-consciousness, factors interrupting tracking, and data inaccuracy are common reasons for discontinued use (14).

Additional risks are increased screen time, perceived stress and excessive exercise and eating behaviors, potentially leading to orthorexia, and eating disorders. Filling out forms about mental health status and lifestyle behaviors may give rise to anxiety and low self-esteem. Not reaching self-identified goals and lack of expected results may cause a feeling of failure and hopelessness. Chat groups may be used to harass other subjects and encouragement and feedback can be misunderstood by subjective interpretation. Ultimately, behavior change will improve clinical values (e.g. blood lipids, metabolic control, blood pressure, pain, and sleep). Individuals on medication would conceivably need to adjust the dose of medication. There is a risk for relapse in behavior change and to re-adjust the medication.

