#### *Exclusion criteria (intervention arms):*

- individuals who are discharged from the app due to refracting the terms of the service
- subjects scoring  $>70$  on well-being will be excluded from the primary analyses (36)
- subjects who appear as friends, colleagues or family with anyone in the research or owner group.

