#### *Exclusion criteria (controls):*

- age  $\leq 17$  years
- is currently using a digital product or any other kind of support for behavior change (e.g. Livsstilsverket, Health Integrator, Weight Watchers).
- is found to be a user of LongLife Active.
- subjects who appear as friends, colleagues or family with anyone in the research or owner group
- subjects scoring  $>70$  on well-being will be excluded from the primary analyses (36).

*Sample size:* The estimation is to reach 5000 consenting individuals in total for the intervention arms and 200 controls.

Total expected duration for each subject's participation: (intervention arms: 24 months, (controls)

*Drop-outs and discontinued use of the digital service:* Subjects who notify they would like to withdraw from the research study are disconnected to the data base. Subjects who discontinue using the digital service will be invited to continue the research participation and to answer the questionnaires online.

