## 7. Statistical design and analysis

### 7.1 Analysis population

For the endpoint well-being an intention-to-treat approach will be applied. By using mixed model for repeated measures all subjects with two or more measurements will be included in the analysis and manual imputation is not needed. For the intermediate outcomes dietary habits, physical activity, and mental health only subjects who have set up change goals within the area will be analysed.

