## 11. Device accountability

Access to the investigated medical device will be controlled using electronic identification (BankID). Subjects in the control group will be excluded if they answer they are using some digital support for behavior change. In addition, a comparison of names and email addresses it will be made to check that the control subjects are not using the investigated medical device.

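### Users discharged from the app are excluded on a post-enrolment event that can occur only in the intervention arms, contrary to the stated intention-to-treat analysis; the control-user exclusion lacks a time point

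*Protocol*

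**What the plan says.** **Discharged users.** The synopsis (Protocol 1.6) says of the intervention arms: "Individuals who are discharged from the app due to refracting the terms of the service will be excluded". The list of exclusion criteria in 6.2.1 repeats it: "individuals who are discharged from the app due to refracting the terms of the service". In the synopsis, the criteria on a WHO-5 score above 70 and on acquaintance with the research or owner group are limited to the primary analyses. The discharge criterion has no such limit.

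**Analysis principle.** Section 7.1: "For the endpoint well-being an intention-to-treat approach will be applied". It adds that the mixed model takes in everyone with at least two measurements.

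**Duration of data contribution.** Section 15 gives two end points for an intervention subject: 25 months after the first registered activity, or a request to withdraw. For controls it gives 7 months after the first questionnaire, or a request to withdraw.

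**Stopping use.** The paragraph on drop-outs at the end of 6.2.1: "Subjects who discontinue using the digital service will be invited to continue the research participation and to answer the questionnaires online".

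**Controls.** The exclusion list in 6.2.1 includes a person who "is found to be a user of LongLife Active". Section 11 describes matching on name and email "to check that the control subjects are not using the investigated medical device", and also says: "Subjects in the control group will be excluded if they answer they are using some digital support for behavior change". Neither the criterion nor the matching is dated.

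**The concern.** An exclusion criterion should rest on what is known at entry. Being discharged for breaking the terms cannot be known then: it needs a subscription and some use of the service. It also has no counterpart among controls, who have no subscription to lose. Applied as written, the rule removes subjects from one side of the primary comparison because of what happened after enrolment, and those removed need not resemble those who stay.

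It may also touch the comparison between levels in hypothesis 2 (section 5.3). Section 4.2 recognises that "Chat groups may be used to harass other subjects", and section 2.2 places the community in Standard and Premium only. Discharges for misconduct in the community, if that is a usual reason, would then fall in those two levels and not in Basic. The protocol does not list reasons for discharge, so this is inference.

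The practical risk is that two analysts following different sections would build different primary datasets, and could be choosing between them after the outcomes are known.

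**Working it through.** The plan gives no figure on this point, so the check is mainly a comparison of sections.

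1. **When discharge can happen.** Entry to the intervention arms is by sign-up and consent (1.6, 6.2.1). Discharge must come later, and only in those arms.

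2. **A worked case.** Table 1 collects WHO-5 at months 0, 1, 3, 6, 12, 18 and 24. A user discharged at month 4 may already have three scores (months 0, 1 and 3).
   - Section 7.1: included, with at least two measurements.
   - Section 15: still contributing, since neither 25 months nor a request to withdraw has been reached.
   - Sections 1.6 and 6.2.1: excluded.

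   These cannot all be followed.

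3. **Why deleting the criterion is not enough.** The model in 7.3 uses months 0, 6, 12, 18 and 24. Of the month-4 user's three scores, only baseline falls on a model time point. Section 6.3.2 says data come primarily through the app, so without another route this user probably supplies nothing at month 6. The online route in 6.2.1 is what would fill the gap.

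4. **Possible size, discharged users.** The protocol gives no discharge rate. Let q be the share of users discharged and D the amount by which their mean falls below that of other users. Excluding them raises the user mean by q × D. Both ranges are assumptions:
   - q = 1%, D = 5: 0.01 × 5 = 0.05 points
   - q = 5%, D = 10: 0.05 × 10 = 0.5 points
   - q = 10%, D = 20: 0.10 × 20 = 2.0 points

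   Against the 12-point target in 7.4 these are 0.4%, 4% and 17%. If discharged users scored higher than others, the sign would reverse.

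5. **Controls.** Two readings of the undated criterion:
   - *Use at entry.* The person was never eligible, and removal after consent does not breach 7.1.
   - *Use at any time.* A control who subscribes at month 3 is removed, while 7.1 (given two measurements) and 15 keep that person in.

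   The text does not settle which is meant.

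6. **Cost of keeping later subscribers as controls.** If a share q of controls subscribes and each gains the full 12 points, with equal prognosis otherwise, the contrast becomes 12 × (1 − q): 11.4 at 5% and 10.8 at 10%. The uptake shares are assumed.

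**The case against.** **The study is not randomised.** Users choose their level (3.1), so there is no randomised comparison to protect. That is correct, and intention-to-treat can here mean only analysis by the level chosen at entry. But the protocol adopts the principle and defines its set, and removal on a later event departs from both. The exclusion of scores above 70 is different, because 7.4 ties it to the baseline score.

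**Discharge by the provider is not the same as a user stopping.** This also stands. The drop-out paragraph in 6.2.1 does not cover discharged users, so there is no contradiction with it. It is relevant because it supplies a follow-up route that can be extended. Nor does the protocol say that data gathered before discharge are deleted.

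**A SAP not shown may settle the handling.** It may fix details, but the protocol itself states both rules, and that conflict remains.

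Four stronger readings are tempting and are not supported:

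- *That the control criterion contradicts intention-to-treat.* It stands among entry criteria, next to one on current use of other support, and section 11 speaks in the present tense. An eligibility check is a fair reading. Only the missing time point is established.
- *That the study itself drives controls to subscribe.* Section 6.2.1 says the app is promoted, and controls are recruited, on social media. It does not say that taking part prompts uptake.
- *That excluding discharged users hides device-related harm.* Section 14 has adverse events and issues logged and discussed by investigators and sponsor, with no link to the analysis set.
- *That a couple of crossovers would be a large share of a 25-person control group.* The 25 in 7.4 is carried into recruitment for each intervention arm; the control target is 200. Even if the plan's 75% drop-out and 20% baseline exclusion applied to controls, 200 × 0.25 × 0.80 = 40 would remain.

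**Conclusion.** The discharge exclusion is a real inconsistency. Sections 1.6 and 6.2.1 remove intervention subjects on an event that can only follow enrolment, while 7.1 and 15 keep the same people in. The conclusion rests on the text and needs no assumed rates.

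Its numerical effect cannot be derived from the protocol. Discharges are probably few; the 0.05-2.0 point range depends wholly on the assumed shares and differences, and the direction is not known. The case for correction is that a rule affecting only one side of the comparison should not stand against the stated analysis set when removing it costs almost nothing.

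For controls the finding is narrower: the criterion and the section 11 check need a date. How to treat controls who subscribe later is partly a choice of estimand, and the protocol should state that choice.

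**What to change.** 1. Delete discharge as an exclusion for the well-being analysis in 1.6 and 6.2.1. Keep these subjects in the level chosen at entry, with all their data.
2. Extend to discharged users the online questionnaire invitation that 6.2.1 gives to those who stop using the service, so that a month-6 value can be obtained.
3. State that the control criterion on being a LongLife Active user, and the matching in section 11, refer to use at the control's baseline questionnaire. A control who subscribes later then stays in the control group, in line with 7.1 and 15.
4. Add a sensitivity analysis that censors such controls at uptake.

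The cost is a few lines of protocol text, a small extension of existing online follow-up, and one sensitivity analysis. The drawback is some dilution of the contrast from controls who take up the app, which the sensitivity analysis would help to show.

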## 2. Identification and description of the investigational device

### 2.1 Identification of the device

LongLife Active AB, 559267-4492 is a Swedish Life Science company based in Täby, Sweden. LongLife Active is the manufacturer of the digital health service LongLife Active® that is a mobile phone application (app) available to download at Google Play and App Store. The development of the investigational device runs in-house at a proprietary Swedish platform in collaboration with an interprofessional scientific advisory board. The scientific advisory board includes independent researchers in the fields of physical activity, nutrition, nursing, psychology, and computer science. Agreements on non-funded collaborations are signed between LongLife Active AB and each researcher. Supplement 2 lists the involved researchers.

LongLife Active® is a digital health service (mobile phone application) classified as a medical software device class I, following Regulation (EU) 2017/745 of the European Parliament and of the Council of 5 April 2017 on medical devices (1). LongLife Active® is managed and regulated following the Swedish standards Medical devices – Quality management systems – requirements for regulatory purposes (ISO 13485:2016), and Health software – Part 2: Health and wellness apps – Quality and reliability (ISO/TS 82304-2:2021).

The digital service is intended for adults (≥18 years) in need of behavioral support to adopt healthy habits and establish a healthy lifestyle. The digital service is independent of any other device. Hence, no external accessories are needed to enable the intended performance and purpose of the device.

The user can connect the digital service with digital activity trackers or an external mobile phone application for automatic registration of the user's physical activity level. All accessories accepted to be synced with the digital service have been regarded within the reported justification of classification and risk class of the medical device. No medical accessories are planned to be connected with the digital service.

The digital service will be further developed to adapt and optimize the behavior support based on user feedback, analytics on user patterns, and inputs from health coaches. Further, it will be updated whenever new guidelines are released e.g. dietary guidelines or work-related and healthcare-based guidelines. To achieve traceability in the development process, new software versions of the investigational device will be assigned version numbers (e.g. version 1.12), and described carefully including detailed information on the adjustments made and the motivation/reason for the adjustments. Study subjects will be informed and directed to upload the new version when published to ensure that all users have access to the latest version. Downloaded software versions during the clinical investigation will be traceable anonymously to all users. The Investigator's Brochure (IB) supplement 3, covers documents and processes that ensure traceability in the development process of the investigational device during the clinical investigation and is available for all parties involved. The Quality manager and CPO at LongLife Active is responsible for maintaining the processes and ensuring traceability during the clinical investigation.

## 2.2 Description of the device

The medical device to be investigated is a digital service aimed to support healthy habits and improve well-being among the general adult population. The digital service includes three core subjects:

1) a Healthy diet, 2) Physical activity, and 3) Mental balance.

The service includes tracking and self-monitoring of behaviors, goal setting, action planning, feedback and digital rewards, a database with food recipes, a database with exercises, inspiration and skills training webinars and articles, and an AI chat. Figure 1 illustrates the core functions of the service.

The included functions and applied behavior change techniques (BCTs) are presented in supplement 4, *Overview functions and BCTs*. Users may sign up for three levels of memberships. The first level (Basic) includes the beforementioned functions, the second level (Standard) also includes a community for social support, and the third level of subscription (Premium) includes a community and the possibility for private health consultations. The number of private health consultations is 3 for a 3 months subscription, 4 for a 6 months subscription, and 6 for a 12 months subscription.

Figure 1. Print screens from the device showing the core intervention components.

The digital service is assisted by artificial intelligence to direct the support to the individual timely and based on each user's needs, motivation, preferences, experiences, opportunities, and capabilities. A literature review undertaken during the development phase showed users of digital services wish for interface design and reminders to be customizable, and that the service is integrated with other services (such as shopping lists) (2). These are aspects that have been regarded to keep engagement over time. With a straightforward design, pictures, and short video instructions the service is customized for people with low skills in the Swedish language or with low digital literacy. Hence, no training or previous experience in digital health services is needed before using

the device. An AI chat is included as a core function to offer individualized support and guidance concerning the user's action plan and goals. Phrases and constructed dialogues of the chat have been developed by health professionals with expertise and experience in health coaching and motivational interviewing.

Based on the risk assessment informative prompts are available in the service to inform the user about realistic goals and actions when adopting a healthy and sustainable lifestyle, and to guide users in need of further support from health professionals. Moreover, report functions are available to alert inappropriate posts in the digital community. Health coaches leading individual- and group counseling in digital video meetings are trained in how to use the investigational device during a mandatory introduction course before operating in the service for the proposed clinical investigation. An introduction course is produced by the Head of health coaching and Quality manager and covers elements of security measures based on the risk assessment. Informed consent, including a description of the data security measures taken is collected from the subject before using the service.

Online technical support is available for all users and health coaches.

The supplement 3 (IB) includes security measures based on the risk assessment and operative guidelines for LongLife Actives health coaches.

### 3. Justification for the design of the clinical investigation

#### 3.1 Rationale for the study design

Digital technologies based on artificial intelligence can provide personalized support for healthy behaviors and empower individuals to actively participate and track their health progress (3-5). The evidence for positive short-term effects of digital technologies on lifestyle change and health outcomes in controlled settings is rigorous (6-11) and using self-monitoring and goal setting as fundamental tools in interventions for behavior change is powerfully advised (9, 10, 12). Well-being is an aspect of health related to the WHO definition of health and is included in sustainable development goal 3 of the Agenda 2030. To the best of our knowledge, the impact of digital technologies promoting healthy habits on *well-being* is not well-studied.

Digital counseling versus simpler interventions using self-monitoring alone has been reported to have an additional effect on behavior change (12). However, the evidence is limited and studies comparing simpler interventions (e.g. providing pedometers or lifestyle advice) with more complex interventions are needed to establish best practices, and for cost-evaluation purposes (6, 12).

When properly designed, digital technologies providing behavior change techniques timely have the potential to improve short-term adherence to healthy behaviors (14, 15). Though, research has until now focused on short-term controlled efficacy trials and up-scaled long-term (> 12 months) implementation studies are rare (10, 12). A major challenge of digital products is high rates of abandonment (13, 14) and factors influencing engagement with digital technology need to be understood and overcome (6, 14). Internalization and implementation factors such as reach and dose, as well as determinants and mediators of efficiency, are rarely researched (5-8, 11). Moreover, real-world trials are needed to establish if digital interventions are effective for behavior change outside the controlled research setting (15, 16).

This study is a real-world post-market observational clinical investigation with a control group aimed to evaluate the impact of a digital service in improving well-being by supporting healthy lifestyle habits. A four-armed control condition will allow comparison between a control group recruited among the general population, and three levels of intervention among subscribers. The levels of intervention are I) core functions include self-monitoring, goal setting, action planning, an AI chat and databases with recipes and exercises; II) the same core functions + social support; II) the core functions + social support + individual counselling by a professional health coach. Randomisation of subjects to the different allocation arms is not appropriate because the users or their employers will pay for the digital service and thus choose the level of support.

